## Abstract

**Background:**

Surgical site infection is the most common complication of abdominal surgery, with a global impact on patients and health systems. There are no tools to identify wound infection that are validated for use in the global setting. The overall aim of the study described in this protocol is to evaluate the feasibility and validity of a remote, digital pathway for wound assessment after hospital discharge for patients in low- and middle-income countries (LMICs).

**Methods:**

A multi-centre, international, mixed-methods study within a trial, conducted in two stages (TALON-1 and TALON-2). TALON-1 will adapt and translate a universal reporter outcome measurement tool (Bluebelle Wound Healing Questionnaire, WHQ) for use in global surgical research (SWAT store registration: 126) that can be delivered over the telephone. TALON-2 will evaluate a remote wound assessment pathway (including trial retention) and validate the diagnostic accuracy of this adapted WHQ through a prospective cohort study embedded within two global surgery trials. Embedded community engagement and involvement activities will be used to optimise delivery and ensure culturally attuned conduct. TALON-1 and TALON-2 are designed and will be reported in accordance with best practice guidelines for adaptation and validation of outcome measures, and diagnostic test accuracy studies.

**Discussion:**

Methods to identify surgical site infection after surgery for patients after hospital discharge have the potential to improve patient safety, trial retention, and research efficiency. TALON represents a large, pragmatic, international study co-designed and delivered with LMIC researchers and patients to address an important research gap in global surgery trial methodology.

**Supplementary Information:**

The online version contains supplementary material available at 10.1186/s13063-021-05398-z.

## Background

### Importance of surgical site infection research

Surgical site infection (SSI) is a global issue. It is the most common healthcare-associated infection in low- and middle-income countries (LMICs) [1, 2] and carries a huge burden to patients, doctors, and health systems around the world [3–5]. Reported rates vary, but SSI is particularly prevalent in abdominal and colorectal surgery; as many as one in three patients get an SSI when the operation involves the large bowel [6]. It was highlighted as the key research priority to improve surgical care worldwide in an international prioritisation process [7] and is the focus of several ongoing global randomised trials [8–11].

### Challenges to assessment of wound infection across settings

The current ‘gold standard’ for diagnosis of SSI in randomised trials is in-person review according to the Centre for Disease Control Criteria at 30 days after surgery by a trained assessor [2]. Hospitals in LMICs treat a high burden of surgical disease [12] and have a high number of eligible patients for recruitment to pragmatic clinical trials. However, in-person assessment is labour and time intensive and requires patients to take additional time-off work and incur costs of travel. This poses particular difficulty in LMICs where patients may live further from a specialist hospital and may already be at risk of financial catastrophe as a result of their index procedure [13, 14]. The SARS-CoV-2 pandemic poses an additional risk where patients are returning to hospital in the perioperative setting [15, 16]. Other methods for assessing SSI are important.

Over 80% of the global population has access to a mobile telephone, opening an opportunity for remote and digital wound assessment pathways [17, 18]. Non-standardised telephone follow-up may risk reducing the validity of outcome assessment. For example, whilst 43% of patients in a prospective cohort study underwent telephone-based assessment, this group had a significantly lower risk-adjusted odds ratio of SSI than those who underwent in-person follow-up [6]. Quality assured methods for remote wound evaluation are urgently required, both to deliver high-quality research and for surveillance after hospital discharge.

### Potential solutions for remote surgical site assessment

The Bluebelle Wound Healing Questionnaire (WHQ) has been developed and validated in the UK (English language) to assess post-discharge infections following abdominal surgery (HTA: 12/200/04) and is attractive for use in randomised trials. The WHQ was designed to be either completed by a healthcare professional or self-reported by patients [19] and as such has been described as a ‘universal-reporter’ outcome measure (UROM) [20]. In a UK validation study, the WHQ demonstrated good reliability and excellent discrimination [21–23]. The WHQ was completed both in-person and over the telephone by a healthcare professional trained in wound assessment (e.g. nurse, junior doctor), demonstrating feasibility of telephone delivery. However, no external validation has been performed in LMICs where health literacy, language and cultural contexts, and digital infrastructure differ substantially. If the WHQ can be administered remotely (e.g. over the telephone) with satisfactory diagnostic accuracy, this would reduce resource usage, making surgical research more effective and more sustainable. Other digital adjuncts to surgical site evaluation such as video assessment may further enhance accuracy [24].

### Justification of study design

Studies within a trial (SWATs) have gained significant attention from trial methodologists and funders over the past 3 years and are now the focus of a Trial Methodology Research Partnership working group (Trial Forge) [25] and National Institute for Health Research (NIHR) funding stream. SWATs exploit the delivery network and infrastructure of major randomised trials to efficiently answer methodological research questions. Ongoing large international trials in global surgery provide a unique opportunity to improve the quality and efficiency of global wound infection research [26].

The overall aim of this study protocol is to evaluate the feasibility and validity of a remote, digital pathway for wound assessment after hospital discharge for patients in low-resource settings.

## Methods/design

### Design summary

Feasibility and diagnostic accuracy of *T*elephone *A*dministration of an adapted wound hea*L*ing Questi*ON*naire for assessment for surgical site infection following abdominal surgery in low and middle-income countries (TALON) is a prospective, multi-centre, international, non-randomised study embedded within a randomised trial, conducted in two phases (TALON-1 and TALON-2). TALON-1 will adapt and translate an outcome measure for use in global surgical research. TALON-2 will validate this adapted outcome measure through a prospective cohort study embedded within two host trials in global surgery.

### Host trials

FALCON is a stratified, pragmatic, multi-centre, 2 × 2 factorial trial testing two measures (skin preparation and antimicrobial sutures) to reduce superficial or deep skin infection following abdominal surgery in seven low- and middle-income countries (NCT03700749) [8]. ChEETAh is a cluster randomised trial evaluating whether the practice of using separate sterile gloves and instruments to close wounds at the end of surgery compared to current routine hospital practice can reduce surgical site infection at 30 days after abdominal surgery [26].

### Reporting and registration

This protocol is reported with reference to recommendations from the Global Health Network for qualitative research in LMICs and Consolidated criteria for reporting qualitative research (COREQ) framework [27, 28], recommendations for best practices in a mixed-methods adaptation of outcome measures [29], and STARD guidelines for diagnostic test accuracy studies [30]. The protocols for the two host trials are reported elsewhere [8, 26]. This SWAT protocol has been pre-registered on the MRC Hubs for Trial Methodology Research Study Within a Trial database [25] (Queen’s University Belfast) (SWAT ID:126).

### Ethics and approvals

The TALON-1 and TALON-2 studies have been approved as an amendment to the host trial protocols by the University of Birmingham Research Ethics Committee (ERN_18-0230_A and ERN_19-0719). The additional risks and ethical implications within TALON-2 were considered very low by the Birmingham Clinical Trials Unit internal review board and international ethics committee. Ethical approval for TALON has been obtained from national, regional, and/or hospital-level ethics committees for selected centres in all participating countries, in accordance with local protocols.

## TALON-1

### Study objectives

To assess patient acceptability, cross-cultural and cross-language equivalence, and content validity of the Wound Healing Questionnaire (WHQ) across LMICsTo assess the scaling and psychometric properties of the WHQ when used across different patient populations and subgroupsTo adapt the WHQ for use in global surgical research by triangulating qualitative and quantitative data

### Study design

TALON-1 will use mixed qualitative and quantitative research methods to explore the cross-cultural and cross-language equivalence of the WHQ across settings, and the acceptability of telephone-based follow-up. Iterative adaptation to the questionnaire will be made, where required, to create an adapted patient-reported outcome measure suitable for use in global trials. The original WHQ prior to adaptation is presented in Additional file 1. Scaling and measurement functioning of the WHQ will be evaluated within a pilot cohort study. Interview data will be triangulated with data about the psychometric properties of the WHQ using Rasch Unidimensional Measurement Modelling.

### Language and local acceptability

All TALON study researchers are fluent in the English language. In some countries, English is a primary or prevalent secondary language amongst the populations that will be recruited to FALCON. In these countries, the feasibility of single-language administration of the questionnaire has been tested at sites within the FALCON trial. Where translation of the WHQ is required, this will be performed using the Mapi process for standard linguistic validation to verify conceptual equivalence across languages and cultures [31–33].

In brief, this involves recruitment and briefing of an in-country consultant to oversee the process in the target country; forward translation by two independent translators native in both the target and source language; production of a reconciled language version with discussion between the translators where warranted; review of the forward translation by the consultant; backward translation into the source language by an independent translator fluent in the target and source language; comparison of the backward translation and original, analysis of discrepancies, and reconciliation with decisions reported and explained; review of the backward translation by the consultant; pilot testing; and finally clinician review.

As the WHQ will be translated into multiple languages, an international harmonisation meeting with the consultants overseeing each language translation will be held after all translations are completed in order to ensure conceptual equivalence in all versions.

### Questionnaire adaptation

Whilst cognitive debriefing with patients is the recommended methodology for cross-language adaptation of an outcome measure [33, 34], modification will be required to progress the study during the SARS-CoV-2 pandemic. As such, adaptation will start with expert review and structured interviews with site researchers. Structured interviews will be conducted with two to three research staff that are participating in the FALCON trial (research nurses, or doctors involved in follow-up) in each participating country in order to ensure cross-cultural relevance of concepts and construct validity of the questionnaire. First, unrefined data from each interview will be reviewed. Second, structured item-by-item summaries will be generated for each interview according to a pre-defined template from the Social Research Association. Third, themes related to comprehension, response mapping, retrieval, and judgement will be extracted with flexibility to include emerging findings. Finally, themes will be categorised for each item to compare and contrast these across interviews. Where required, iterative adaptation will be made until a point of saturation according to accepted best practice principles for adaptation of instruments [29, 33, 35].

Further iterative adaptation will be performed using cognitive interviews undertaken face-to-face with patients if this is safe and practicable. Otherwise, adaptation will use data from site researchers only, with this limitation noted in study outputs. Interview data will be used to explore content, conceptual and cross-cultural equivalence of the global WHQ in greater depth [35]. Data will be collected up to the point of saturation; we anticipate approximately 6 to 8 patients per country will be sufficient. Adult patients (> 18 years) that have undergone intra-abdominal surgery of any urgency and through any operative approach will be recruited from surgical assessment areas, inpatient wards, and outpatient clinic settings. Informed consent for inclusion will be taken and recorded within a dedicated Informed Consent Form. A specific Patient Information Sheet for TALON-1 will be provided. Purposive sampling will include patients from each included country, those who have and have not suffered an SSI, urban and rural hospital settings, and high school level of education and lower education level. The results of cognitive debriefing will be reviewed to assure cultural relevance and equivalence. Comparison of patients’ interpretation of the translation and the original version will be highlighted to amend discrepancies.

### Psychometric testing and scaling

Pilot administration of the WHQ will be performed in adult patients undergoing abdominal surgery and recruited to the host trials, over the telephone by a non-surgeon clinician; this can be a research nurse, non-surgeon physician, or other delegated members of the site research team. Non-surgeon physicians will be trained to deliver the WHQ by a member of the study management group. Monitoring of the first 10 patients followed up over that telephone at each site will be performed for quality assurance. Content, construct validity, and unidimensionality of the WHQ will be tested using Rasch analysis [36]. The Rasch unidimensional measurement model will examine the psychometric properties of the WHQ, identify anomalies in the data, and evaluate the extent to which the WHQ items are measuring wound infection [37, 38]. Differential item functioning will be tested for equivalence by country, language, age (young age (18–29)/middle age (30–59)/older age (> 60 years)), and sex (male/female) groups. A target of at least 100 patients per language and per country will be set for data included in the Rasch analysis [39].

Data sources will be triangulated using data (i.e. between countries) and methodological (i.e. between qualitative interviews and psychometric analysis of quantitative pilot data) triangulation to support the final adaptation of the WHQ across each included language [29, 40–43]. This will be followed by proofreading, before completion of a final report and publication of the adapted WHQ.

### Community engagement and involvement

Community engagement and involvement with patients and members of the public from LMICs will be engaged in all phases of the design and delivery of TALON-1. The interview topic guide will be co-designed with input from a representative global surgery patient forum. Practicable methods for conducting interviews, and patient compensation for the time in participation will be determined with the support of local community leaders. The Guidance for Reporting Involvement of Patients and the Public (GRIPP-2) short form will be used to track and report the impact of community engagement and involvement (CEI) within this study [44].

### Ethical considerations and data handling

All participant data for TALON-1 will be fully anonymised and unlinked and stored securely within a password-protected NVivo V12 data management system.

TALON-1 will therefore produce a globally adapted Wound Healing Questionnaire, suitable for use in global surgery research, including the TALON-2 validation study.

## TALON-2

TALON-2 will be a cohort study within the FALCON and ChEETAh trials to test the feasibility and accuracy of telephone administration of the adapted WHQ in the diagnosis of surgical site infection.

### Study objectives

To evaluate the diagnostic accuracy of telephone administration of the WHQ in detection of abdominal surgical site infection across LMICsTo assess the feasibility of delivery of the telephone WHQ by a non-surgeon researcher within the FALCON trialTo assess the feasibility of live wound videography (or wound photography) as a diagnostic adjunct for telephone-based wound follow-up

### Centre selection

Centres for TALON-2 will be chosen based upon (1) the proportion of recruited patients that are likely to return for routine in-person 30-day follow-up and (2) the site’s ability to have an independent non-surgeon researcher perform telephone follow-up for TALON-2 that will not perform in-person, 30-day follow-up. Sites will be selected from across seven low- and middle-income countries (Fig. 1).

**Fig. 1 Fig1:**
[figure not shown]
Map of participating countries. Participating countries marked in red

### Eligibility criteria

Consecutive adult patients (greater than 18 years) recruited to the FALCON or ChEETAh study that are likely to return for routine in-person follow-up at around 30 days postoperatively are eligible. Consent for an additional telephone follow-up call within the TALON-2 study will be taken at the same time as trial consent, using a targeted Informed Consent Form and Patient Information Sheet. Community representatives will co-produce these resources to ensure culturally appropriate language and delivery.

### Study intervention

Telephone-based administration of the WHQ will be compared to the ‘gold standard’ (reference test) of in-person assessment at 30 days after surgery by a trained clinician in accordance with the US Centre for Disease Control criteria (Additional file 2). The WHQ will be delivered integrated into the trial pathway for included patients (Fig. 2). The telephone-based WHQ will be performed at 28–30 days (i.e. in the 72 h prior to in-person follow-up) by a non-surgeon researcher, according to a telephone script. Patients will be asked to provide between one and three telephone contact numbers, either personal or belonging to a family member or community worker. The non-surgeon researcher directing completion of the WHQ should be blinded to the outcome of the in-person wound assessment within the FALCON trial. In the event that the patient is unable to be contacted by telephone at 27–30 postoperative days (before in-person follow-up), the WHQ can be performed after the in-person follow-up appointment, where possible. This should be completed by a non-surgeon researcher that is independent of the assessment for the FALCON primary outcome, to ensure independent measures are taken. The process and pathway for telephone follow-up will be co-designed by patient and public partners to optimise successful and culturally sensitive delivery.

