### Sample size

As TALON-2 is a validation study for a diagnostic criterion, no formal sample size calculation is required. A range of sample sizes and their impact on the 95% confidence interval (CI) around estimates of sensitivity 0.92 and specificity 0.95 based on a prevalence of 0.21 using the binomial exact formula are presented in Table 1. Sample sizes are adjusted to allow for 15% loss to follow-up from the host trials, and 15% of patients who do not achieve both telephone WHQ completion and 30-day in-person follow-up within TALON-2. Sampling from Hub and Spoke centres across several LMICs will give a representative sample of urban and rural settings.

**Table 1 Tab1:** TALON-2 study sample size estimates

Patients recruited to host trial	Patients retained for follow-up	Paired WHQ and in-person follow-up	Patients with SSI^a^	Patients without SSI^b^	Precision around test accuracy measures	
					Sensitivity (95% C.I.)	Specificity (95% C.I.)
714	607	516	108	408	0.92 (0.85–0.96)	0.95 (0.93–0.97)
571	485	412	87	325	0.92 (0.84–0.97)	0.95 (0.92–0.97)
428	364	309	65	244	0.92 (0.83–0.97)	0.95 (0.92–0.97)
285	242	206	43	163	0.92 (0.81–0.99)	0.95 (0.91–0.98)

^a^0.21 * number paired WHQ and in-person follow-up

^b^0.79 * number paired WHQ and in-person follow-up

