There are limitations to the proposed study design. Firstly, due to limitations with travel around the SARS-CoV-2 pandemic, the ability to conduct cognitive interviewing during the adaptation and translation process may be limited. From site researchers and CEI representatives, it was highlighted that video-based interviews with patients in low-resource settings may prove challenging both logistically, and to the richness of the data, and risk of accentuating power imbalances between the researcher and patients. We have modified the proposed methodology to include pragmatic, structured interviews with site researchers; however, further iterative adaptation following face-to-face patient interviews may be required in the future [29]. A mixed-methods approach, including Rasch analysis of pilot cohort data, will further enhance the adaptation and scaling process [68]. Secondly, the Wound Healing Questionnaire has not previously been validated for use across low-resource settings, as such the optimal score calibration is yet to be determined. Whilst a pre-defined range of cut points will be adopted, this combines the calibration and validation phases into a single analysis; this was a pragmatic decision to manage a complex project across global trials in a manageable timeframe. Thirdly, we have not pre-defined thresholds for sensitivity and specificity for that would be acceptable for clinical practice or trial adoption in this protocol. Consensus work is required to define minimally acceptable criteria for diagnostic accuracy during future development and implementation of the WHQ [69]. Fourthly, the WHQ can be administered any time during the 72 h preceding in-person assessment. Whilst there is a theoretical risk that patients could suffer a new SSI event 28 to 30 days after surgery that has not previously manifested, this is clinically improbable and is not supported by existing data [6, 70]. Another risk is that completion of telephone follow-up immediately prior to in-person follow-up may have a deleterious effect on in-person follow-up rates, overestimating the retention benefit. We have designed the TALON case report form and patient information to stress the need for both in-person and telephone follow-up, and can compare rates of attrition to the overall host trial population. Finally, the exploratory use of video follow-up in this study is not the central focus of this work. Whilst this will provide the first available data on video-based follow-up of surgical wounds in LMICs, contributing significantly to understanding of this area, further work is likely to be required to standardise protocols for ‘live’ video assessment and explore its reliability in depth.

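### Telephone questionnaires taken after the in-person reference visit are not kept out of the primary accuracy estimate and may bias it, probably upward

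*Protocol article*

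**What the plan says.** The Study intervention section of the protocol article sets the planned order: "The telephone-based WHQ will be performed at 28–30 days (i.e. in the 72 h prior to in-person follow-up"). It then makes an exception. For a patient "unable to be contacted by telephone at 27–30 postoperative days" before the visit, "the WHQ can be performed after the in-person follow-up appointment, where possible". No last day for the late call is given.

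The same section protects the measurement on the caller's side. The researcher should be blinded to the in-person result, works from a telephone script and, for late calls, must be independent of the person who assessed the host-trial outcome. Nothing there deals with what the patient has learned by then.

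The primary outcome (Primary outcome measure) compares the telephone WHQ with in-person review and sets no condition on their order. The Sample size section sets aside "15% of patients who do not achieve both telephone WHQ completion and 30-day in-person follow-up within TALON-2", so a pair is defined by completion of both assessments and not by their sequence. The Statistical analysis section cross-tabulates a dichotomised self-assessment score against the CDC diagnosis, again without separating late questionnaires.

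The limitations paragraph of the Discussion describes the timing differently: "the WHQ can be administered any time during the 72 h preceding in-person assessment". It does not mention the post-visit route.

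**The concern.** In a diagnostic accuracy study the index test should be read without knowledge of the reference result. Here the index test is a patient's report, so blinding the caller is only half of the protection. Once the visit has taken place, a trained clinician has looked at the wound, and the patient may have been told whether it is infected or been treated for it. The answers given afterwards can partly echo the reference standard.

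The study asks whether a remote call can stand in for a visit. A questionnaire answered after an examination does not test that. If such pairs are pooled with the others, sensitivity and specificity no longer describe the remote pathway alone.

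Two related weaknesses follow. The limitations paragraph defends the timing only for calls before the visit, so the one route that reverses the test order is never discussed. The pre-visit window is also not fixed: the same section gives days 28–30, a 72-hour interval before the visit, and days 27–30. Two of these count from surgery and one from the visit, which the Eligibility criteria place only at around 30 days.

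**Working it through.** **1. The plan's own figures.** The Sample size section works from "estimates of sensitivity 0.92 and specificity 0.95 based on a prevalence of 0.21 using the binomial exact formula". It also states: "Sample sizes are adjusted to allow for 15% loss to follow-up from the host trials". A further 15% is removed for incomplete pairs.

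- Attrition, first row of Table 1: 714 × 0.85 = 606.9 (607); 607 × 0.85 = 516.0 (516).
- Split by prevalence: 0.21 × 516 = 108.4 (108 with SSI); 0.79 × 516 = 407.6 (408 without).
- Clopper–Pearson 95% limits with whole counts: 99/108 gives 0.848–0.961 (printed 0.85–0.96); 388/408 gives 0.925–0.970 (printed 0.93–0.97).

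The first row reproduces, and the other rows agree to rounding. Table 1 is not in question.

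**2. Size of an upward shift.** Let f be the share of paired questionnaires taken after the visit, assumed equal in patients with and without SSI. The article does not give f. Treat the planning values as the accuracy of pre-visit calls.

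Pooled accuracy = (1 − f) × pre + f × post, so the shift is f × (post − pre). It is largest when every late questionnaire agrees with the visit (post = 1):

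- sensitivity: f × (1 − 0.92) = 0.08f
- specificity: f × (1 − 0.95) = 0.05f

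| Assumed f | Pooled sensitivity, ceiling | Pooled specificity, ceiling |
|---|---|---|
| 5% | 0.924 | 0.953 |
| 10% | 0.928 | 0.955 |
| 20% | 0.936 | 0.960 |
| 30% | 0.944 | 0.965 |

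At f = 20% the ceiling is 1.6 points for sensitivity and 1.0 point for specificity.

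The general ceiling is f × (1 − pre), so it rises as true accuracy falls. If pre-visit sensitivity were 0.80 (an assumption, not a protocol figure), it would be 0.20 × 0.20 = 0.04, or 4 points, at f = 20%.

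**3. A downward shift is also possible.** Suppose late calls agree less well because the wound healed or was treated before the call, with assumed post-visit values of 0.85 and 0.90. Then f = 10% gives 0.913 and 0.945, and f = 20% gives 0.906 and 0.940.

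**4. Precision if late pairs leave the primary set.** First row of Table 1, exact limits with the proportions held at 0.92 and 0.95 (fractional counts):

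| Assumed f | With SSI | Sensitivity limits | Without SSI | Specificity limits |
|---|---|---|---|---|
| 0 | 108 | 0.852–0.963 | 408 | 0.924–0.969 |
| 10% | 97 | 0.847–0.965 | 367 | 0.922–0.970 |
| 20% | 86 | 0.841–0.968 | 326 | 0.920–0.971 |
| 30% | 76 | 0.835–0.970 | 286 | 0.918–0.972 |

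At f = 20% the sensitivity interval widens from 0.963 − 0.852 = 0.111 to 0.968 − 0.841 = 0.127.

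**The case against.** The best defence is that the article never says late questionnaires enter the primary estimate. It refers to a full analysis plan published online, which is not among the documents here, and defining the analysis set is ordinary content for such a plan. This stands in part. A reader might infer that the plan deliberately counts these pairs. The text supports only that nothing shown excludes them, so that pooling is what happens by default. The contradiction between the intervention section and the limitations paragraph lies within the article and needs correcting there whatever the analysis plan says.

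A reader might also infer that accuracy is necessarily inflated. The documents do not establish that. Knowledge of the diagnosis would push agreement up, but an open-ended delay, healing or treatment could push it down, as step 3 shows. Nor do they show that the shift is large. At the planning values the ceiling is modest, the share of late calls is unknown, and collecting up to three telephone numbers per patient should help to keep it low.

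It would also be wrong to say that the design has no safeguard beyond an independent caller: blinding and a script are specified. They do not reach the patient.

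Finally, one might want late questionnaires removed from the retention ratio, because attenders get a second chance to return one. But the Secondary outcome measures count any returned telephone WHQ, and a fully remote pathway could also call again after day 30. Simply dropping them could understate telephone retention. The 28–30 against 27–30 mismatch is a one-day inconsistency that needs tidying and carries little weight by itself.

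**Conclusion.** The point holds in a limited form and should be fixed; confidence is medium. The protocol permits the index test after the reference test without a time limit, protects the caller but not the patient from the reference result, and sets no order condition on a pair in any section shown. The accuracy estimates may therefore be biased, probably upward. At the planning values the upward shift cannot exceed 0.08f for sensitivity and 0.05f for specificity; it could be larger if true accuracy is lower, which is possible because the WHQ has not been validated in these settings. These figures assume that pre-visit calls perform at the planning values and that f is the same with and without SSI. Neither f nor the accuracy of late calls is given in the article, so both direction and size stay open until the late calls are counted.

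**What to change.** - Base the primary accuracy analysis on questionnaires completed before the in-person assessment, under one window anchored to the recorded visit date. Reconcile days 28–30, days 27–30 and the 72-hour interval to it.
- Record the order of the two assessments and the interval between them, and report how many questionnaires were late.
- Include late questionnaires in a labelled sensitivity analysis of accuracy.
- Report the retention ratio with and without post-visit questionnaires.
- Correct the limitations paragraph so that it acknowledges the post-visit route.

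The cost is wording, plus some precision. At an assumed 20% late share, 86 patients with SSI and 326 without remain in the first row of Table 1; the sensitivity interval becomes about 0.84–0.97 against the printed 0.85–0.96, and the specificity interval about 0.92–0.97 against 0.93–0.97. Some harder-to-reach patients also leave the primary set, which may alter its case mix; the sensitivity analysis would show whether that matters.
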